### Anthropometry

The following anthropometric measures will be taken at baseline, end-program and at the 24-month follow up: standing height (Leicester Height Measure, Invicta Plastics, Oadby, Leicester, United Kingdom) and mass (Tanita UM-108, Tanita Corporation, China), waist and hip girths, skin fold measurements (triceps, biceps, subscapular and iliac crest) and thee dimensional (3D) whole-body laser scans (Vitus Smart XXL, Human Solutions GmbH, Kaiserslauten, Germany). All physical measurements will be taken according to the International Standards for Anthropometric Assessment
[36]. Intra-tester technical error of measurement (TEM) (in a mixed population) is reported as <5.0% for skinfolds and <1.0% for other measures
[37]. Inter-tester technical error of measurement (in a mixed population) compared to a criterion anthropometrist is reported as <7.5% for skinfolds and <1.5% for other measures
[37]. Measurements extracted from the 3D scans will include girths, as well as segmental and whole body volumes, which will be taken according to the procedures described in Schranz et al. (2010)
[38]. Using the hardware-software suite used in this study, scan-extracted girths and volumes have been reported to demonstrate good test-retest reliability (typical error <1.6%) and accuracy (typical errors <1.8%) relative to physical measurements (girths), water displacement plethysmography (segmental volumes) and underwater weighing (whole body volume)
[39,40].

### Physiological measures

Several physiological measures will be collected at baseline and end-program: blood pressure, total serum cholesterol and fasting blood glucose. Blood pressure will be measured using a non-invasive automated sphygmomanometer (Dinamap Pro 100, GE Medical Systems Information Technologies and Critkon Company, LLC, United Kingdom). Blood pressure will be repeatedly measured until there are two measurements within 5 mmHg for both systolic and diastolic pressure. Total serum cholesterol and fasting blood glucose will be measured using a finger-tip blood sample with automated lancets (Accu-Check Safe-T-Pro Plus, Roche, Australia). Blood specimens will be processed using a Reflotron Plus analyser (Woodley Equipment Company Limited, United Kingdom). Participants will be instructed to be rested and fasted for a minimum of 12 hours prior to the physiological measures.

### Cardiorespiratory Fitness

VO2_max_ will be estimated at baseline and end-program using the Physical Work Capacity 75% (PWC75%) sub-maximal bicycle ergometer test
[41]. The sub-maximal test will be carried out using an electronically braked cycle ergometer (Ergoselect 200, Ergoline, Germany) and a heart rate monitor and transmitter unit (Polar S160i, Polar, Finland). The test involves 3 x 3-minute stages with progressively increasing resistance, lasting a total of nine minutes (excluding warm-up). The final workload aims to elicit a heart rate that is close to 75% of the participant’s age-predicted maximal heart rate (where predicted HR_max_ = 220 minus age of participant). A linear regression equation then allows an estimate of the maximal workload at the participant’s predicted maximal heart rate.

### Statistical analysis

As this study is aiming to address a mechanism rather than test the effectiveness of the exercise intervention, analysis will be carried out on a per protocol basis where only those participants who complete the intervention will be included in the analyses. Subsequent analyses will also be carried out based on 50% and 75% compliance thresholds with the prescribed volume of physical activity according to objectively monitored adherence (based on heart rate monitoring).

Socio-demographic and anthropometric data will be analysed descriptively. Baseline characteristics of the three groups will be presented but not formally tested for differences. Random effects mixed modelling will be used with time (0, 3, 6, 12 and 24 weeks) and group allocation (*Control, Moderate, Extensive)* as the fixed factors. A time by group interaction term will be used to formally test the differences between the groups. Alpha will be set at 0.05. The response variables for the primary analysis investigating the activitystat hypothesis will be total and activity energy expenditure derived from doubly labeled water, resting metabolic rate derived from indirect calorimetry, total counts and minutes spent in sedentary, light and MVPA derived from accelerometry and minutes spent in MVPA, physical activity superdomain and physical activity level derived from the MARCA.

Response variables for secondary analyses will include use of time derived from the MARCA to determine how participants adjust their daily activity patterns when commencing an exercise program and anthropometric (height, mass, girths, skin folds, volumes) and physiological variables (blood pressure, fasting blood glucose and total serum cholesterol, VO_2max_) to investigate dose response relationships between physical activity and anthropometric and physiological variables.

A priori power calculations determined that a sample of 26 participants per group (n=78) should be able to detect small to moderate effect sizes (Cohen’s d=0.2-0.6) for within groups (time effect) and group x time interactions, at 5% alpha level and 80% power. Due to documented dropout rates of physical activity interventions
[4] and the intensive assessment protocol for this study, a dropout rate of 25% will be anticipated and therefore a total of 46 participants per group (n=138) will be recruited.

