[13]. Given that the time period over which a supposed activitystat operates is currently unclear, the study should employ a sufficiently long stimulus with regular measurement periods to help identify the time course of compensation. Furthermore, the stimulus should be of a sufficient strength to induce compensation. Ideally this would include multiple physical activity stimuli of different strengths to allow investigation of the threshold of the activitystat mechanism. Compliance with the stimulus should be monitored and a per-protocol analysis should be employed, given that the study’s purpose is to test the mechanism of the activitystat and not the effectiveness of an intervention. Participants must also not be at the extremes of very active or very sedentary. Participants who are very active may demonstrate a “ceiling effect” with neither the time nor the drive to add further physical activity to their schedules. Very inactive participants may demonstrate a “floor effect” where they may have insufficient physical activity in other domains to trade off against the imposed physical activity program. Finally, a randomised controlled trial design should be employed to account for the possibility of dynamic setpoints (due, for example, to maturation
[14] and season
[15]). To date, there is no study that comprehensively covers this methodological framework.

Therefore, this paper presents a protocol specifically designed to test the activitystat hypothesis in adults, taking into account these key methodological considerations. The primary aim of this study is to determine the effect of two different imposed 6-week exercise loads in previously sedentary 18–60 year olds on total energy expenditure and physical activity. The secondary aims of this study are (a) to determine how participants adjust their daily activity patterns to accommodate the imposed exercise load, and (b) to investigate dose–response relationships between physical activity and anthropometric and physiological variables.

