### Intervention

The two intervention conditions are based upon a six week group-based physical activity intervention - a program previously developed and tested within the University of South Australia, known as the 40-DAY Physical Activity Program
[18]. The program comprises both group-based, instructor-led and self-directed individual exercise sessions with progressive increases in exercise intensity. The two intervention conditions involve similar types of physical activities and intensities, and differ only in volume. The group sessions are graded in intensity and are designed to expend approximately 800 kJ in the first week and to increase by about 200 kJ per session in each subsequent week.

This intervention was designed within the framework of several theoretical components important for long-term behavioural change, including an intra-personal focus on self-efficacy, outcome expectancy of health and fitness benefits, inter-personal and cultural factors (group work), physical activity monitoring, goal setting, identifying barriers and enablers and health and fitness testing
[18]. An expanded explanation of the methodological considerations of the intervention design is available in the paper by Norton and colleagues
[18].

The Moderate intervention is designed to involve approximately half the load of the Extensive group. Participants in the Moderate group will attend instructor-led group classes of 60 minutes duration three times per fortnight. Participants will then be required to carry out a minimum of 30 minutes of self-directed activities on a further two days per week. The Moderate exercise intervention is designed to increase MVPA by approximately 150 minutes per week (equivalent to approximately 4000 kJ/week). This dosage is consistent with the minimum level of energy expenditure recommended for exercise beginners by the United States Surgeon General (600 kJ/day)
[19]*.* Table
1 shows the activities and the progressive increase in planned energy expenditure during the intervention for the Moderate group.

**Table 1 T1:** Moderate group physical activity itinerary (grey shading indicates group exercise session)

	**Sunday**	**Monday**	**Tuesday**	**Wednesday**	**Thursday**	**Friday**	**Saturday**
**Week 1 600 kJ/session**					Introductory circuit involving stretching and body awareness activities such as climbing, rolling, balancing, hopping, using a range of different surfaces.	Individual exercise session	Individual exercise session

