**Week 2 700 kJ/session**			Training circuit with light hand-held weights, step-ups, stair climbing (one flight), fit ball and core stability exercises.	Individual exercise session	Circuit training including light resistance with dumbbells and medicine ball activities, dynamic stretching activities, introduction to boxing and skipping.		Individual exercise session
**Week 3 800 kJ/session**		Individual exercise session	Resistance class with hand-held dumbbells or light barbells (<10kg), dynamic stretching, resistance routines.		Outdoor circuit training including walking with hand-held weights, stair and hill climbing and introduction to jogging.		Individual exercise session
**Week 4 900 kJ/session**			Circuit training including dynamic stretching activities, resistance activities, spin class, boxing.		Individual exercise session		Kayaking in two-person sit-on-top kayaks ~1.5 hours’ duration
**Week 5 1000 kJ/session**		Individual exercise session	Outdoor team games- modified soccer or lacrosse.		Circuit training including dynamic stretching activities, resistance activities, jogging or stair climbing, spin class.		Individual exercise session
**Week 6** **1200 kJ/session**	Group bush walk ~1.5-2 hours duration	Individual exercise session			Sand dune and beach activities: walking or jogging through sand hills, team games on beach.		

Participants in the Extensive group will attend instructor-led group classes of 60 minutes duration three times per week. Participants will then be required to carry out a minimum of 30 minutes of self-directed activities on a further four days per week. The extensive exercise intervention is designed to increase MVPA by approximately 300 minutes per week (equivalent to approximately 8000 kJ/week). Overall, participants will be required to complete at least 30 minutes of activity every day for 40 days. Table
2 shows the activities and the progressive increase in planned energy expenditure during the intervention for the Extensive group. To reflect the modified nature of the 40-day program in this study for the Moderate exercise group, the intervention conditions will now be referred to as the UniSA Physical Activity (PA) program.

**Table 2 T2:** Extensive group physical activity itinerary (grey shading indicates group exercise session)

	**Sunday**	**Monday**	**Tuesday**	**Wednesday**	**Thursday**	**Friday**	**Saturday**

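### The only test given for the dose-response aim treats the three arms as unordered, so a significant result cannot by itself support a dose-response statement

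*Protocol article*

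**What the plan says.** In the Protocol article, the last paragraph of Background gives secondary aim (b) as "to investigate dose–response relationships between physical activity and anthropometric and physiological variables". Statistical analysis repeats it for the secondary response variables, which are there "to investigate dose response relationships between physical activity and anthropometric and physiological variables".

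The Intervention section sets the arms out as a dose scale. Moderate is "designed to increase MVPA by approximately 150 minutes per week". For the other arm, "The extensive exercise intervention is designed to increase MVPA by approximately 300 minutes per week". Control receives no exercise program during the study.

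The model under Statistical analysis is: "Random effects mixed modelling will be used with time (0, 3, 6, 12 and 24 weeks) and group allocation", with Control, Moderate and Extensive as the levels of group. The test is "A time by group interaction term will be used to formally test the differences between the groups", and "Alpha will be set at 0.05". The section names no ordered contrast, dose score, Extensive-versus-Moderate comparison or regression on measured activity.

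Blood pressure, cholesterol, glucose (Physiological measures) and estimated VO2max (Cardiorespiratory Fitness) are measured at baseline and end-program only. Anthropometry has one further follow-up visit.

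**The concern.** With group as a categorical factor, the null hypothesis of the interaction is that all three arms change alike. Any departure counts against it, whatever the order of the arms. A dose-response question is narrower: does the outcome move with dose, and does the larger dose do more than the smaller one? A significant interaction is also what one expects if 150 and 300 minutes work equally well, or if the smaller dose works better.

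Two things are at stake. A significant interaction on a secondary outcome could be read as dose-response when it does not show one. And if a true linear response exists, a test that ignores the order of the arms gives up power that the design already provides.

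**Working it through.** **Inputs from the Protocol article.** Three arms at designed doses 0, 150 and 300 min/week; alpha 0.05; two visits for the physiological outcomes and VO2max; 26 per group from the power statement; 46 recruited per group with 25% dropout, so 46 × 0.75 = 34.5, taken as 34.

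**Assumptions.** The maximum arm effect is d = 0.6 SD of the change score, with equal SDs across arms. The value 0.6 is the top of the plan's stated effect-size range; reading it as SD of change is my choice. The plan's 26 per group cannot be reproduced uniquely, because it gives neither a correlation nor the number of visits behind it, so 26 serves here only as a sample size.

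**Step 1: the interaction at two visits.** It is the one-way F test on change scores, with 2 and 3n − 3 degrees of freedom and noncentrality λ = n × Σ(μᵢ − μ̄)² / SD².
- Linear (0, d/2, d): the deviations are −d/2, 0, d/2, so λ = nd²/2.
- Moderate and Extensive swapped (0, d, d/2): the deviations are the same in another order, so again λ = nd²/2.
- Plateau (0, d, d): the deviations are −2d/3, d/3, d/3, so λ = 2nd²/3.

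The ranking therefore does not depend on n, SD or d.

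**Step 2: numbers for d = 0.6.** At n = 26, λ = 26 × 0.36/2 = 4.68 (linear or swapped) and 2 × 26 × 0.36/3 = 6.24 (plateau). At n = 34, λ = 6.12 and 8.16.

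**Step 3: one-degree-of-freedom contrasts.** With weights (−1, 0, 1), the noncentrality is δ = (μ_E − μ_C)/(SD × √(2/n)). This is 0.6/√(2/26) = 2.16 at n = 26 and 0.6/√(2/34) = 2.47 at n = 34. Extensive minus Moderate has the same form with μ_E − μ_M, so a true difference of 0.3 gives δ = 1.08 and 1.24.

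| True pattern (SD of change) | Interaction, n = 26 / 34 | Linear contrast, n = 26 / 34 | Extensive minus Moderate, n = 26 / 34 |
|---|---|---|---|
| Linear (0, 0.3, 0.6) | 46% / 58% | 57% / 69% | 19% / 23% |
| Swapped (0, 0.6, 0.3) | 46% / 58% | 19% / 23% | 19% / 23%, favouring Moderate |
| Plateau (0, 0.6, 0.6) | 58% / 71% | 57% / 69% | 5% / 5% |

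For a true linear response the interaction loses 57 − 46 = 11 and 69 − 58 = 11 points against the linear contrast.

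**Step 4: sensitivity.** A 20,000-run simulation at n = 26 and d = 0.8 gave 72% (linear), 72% (swapped) and 84% (plateau) for the interaction; the noncentral F gives 72%, 72% and 84%. With three visits, as for anthropometry, and assuming correlation 0.5, d = 0.8 and half the effect kept at follow-up, the figures are 61%, 61% and 75%. The ranking holds.

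**Step 5: what a linear contrast cannot do.** It handles order but not the plateau: its rejection rate is the same 57% / 69% under both patterns, because with equal spacing it is simply Extensive minus Control. Adding a rule that Extensive minus Moderate must have the same sign does not repair this. Under the plateau (0, 0.6, 0.6) that rule declares a dose-response in about 37% / 42% of simulated trials. Requiring both contrasts to be significant brings this down to about 2%, but cuts power for the true linear response to about 16% / 21%.

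**The case against.** The strongest objection is that this is close to absent detail. The interaction is said to test differences between groups, and it does. The sentence comes before the list of primary variables, and the paragraph on secondary variables gives a purpose but no test. Follow-up contrasts are often left to a fuller analysis plan. This stands in part: applying the interaction to aim (b) is an inference. But the model, test and alpha sentences are not restricted to the primary variables and no other method is named, so the one test on the page does not match the aim on the same page.

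Second, the aim speaks of physical activity, which could mean measured volume, for example from the heart-rate monitors, rather than assigned arm. That reading is open, and the fix has to cover it.

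Third, the 0, 1, 2 spacing is not beyond doubt. Counting sessions in Tables 1 and 2 as extracted and multiplying by the kJ labels gives 18,100 kJ for Moderate (3×600 + 4×700 + 4×800 + 3×900 + 4×1000 + 3×1200) and 44,000 kJ for Extensive (6×600 + 7×800 + 7×1000 + 7×1200 + 7×1400 + 6×1600), a ratio of 2.4. A categorical factor imposes no shape and is a defensible model. That supports keeping the model; it does not make the omnibus test an answer about dose.

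Two stronger readings are tempting. One is that the investigators will report a significant interaction as a dose-response; the article never says so. The other is that the analysis cannot compare Extensive with Moderate; the fitted model does estimate each arm's change, and what is missing is a stated contrast.

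**Conclusion.** The point holds as a mismatch between a stated aim and the only stated test. A significant time-by-group interaction cannot, by itself, support a dose-response statement for the anthropometric and physiological outcomes. That it rejects equally often when Moderate and Extensive are swapped, and more often for a plateau than for a linear response with the same maximum effect, is algebra and needs no assumption about sample size or effect.

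The percentages are illustrative. They rest on 0.6 SD of change, two visits and 26 or 34 completers per arm. On that basis the cost under a true linear response is about 11 points of power. The aim is secondary and the remedy is wording, so this is a change that should be made; it is not a threat to the trial's primary question.

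**What to change.** For the anthropometric and physiological outcomes, keep the mixed model and pre-state two contrasts of change from baseline to end-program:

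1. A linear dose contrast on the designed doses of 0, 150 and 300 min/week, noting that with equal spacing it equals Extensive minus Control.
2. Extensive minus Moderate, reported with its 95% CI.

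Limit any statement that more exercise does more to what the second interval supports. Do not use a same-sign rule. If the aim is meant to concern measured activity, say so, and present a regression on heart-rate-monitored volume as a supportive, non-randomised analysis.

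The cost is analysis wording, with the same data and the same model. There are two downsides. The linear contrast is less sensitive to non-monotone patterns than the interaction. Extensive minus Moderate has low power, about 19% / 23% for a true difference of 0.3 SD at 26 / 34 per arm, so it should be read mainly as an estimate with its interval, and a non-significant result should not be taken as evidence that the two doses are equivalent.

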**Methods:**

This study will be a randomised, multi-arm, parallel controlled trial. Insufficiently active adults (as determined by the Active Australia survey) aged 18–60 years old will be recruited for this study (n=146). Participants must also satisfy the Sports Medicine Australia Pre-Exercise Screening System and must weigh less than 150 kg. Participants will be randomly assigned to one of three groups using a computer-generated allocation sequence. Participants in the *Moderate* exercise group will receive an additional 150 minutes of moderate to vigorous physical activity per week for six weeks, and those in the *Extensive* exercise group will receive an additional 300 minutes of moderate to vigorous physical activity per week for six weeks. Exercise targets will be accumulated through both group and individual exercise sessions monitored by heart rate telemetry. Control participants will not be given any instructions regarding lifestyle. The primary outcome measures are activity energy expenditure (doubly labeled water) and physical activity (accelerometry). Secondary measures will include resting metabolic rate via indirect calorimetry, use of time, maximal oxygen consumption and several anthropometric and physiological measures. Outcome measures will be conducted at baseline (zero weeks), mid- and end-intervention (three and six weeks) with three (12 weeks) and six month (24 week) follow-up. All assessors will be blinded to group allocation.

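### The article gives three different accounts of the primary outcome, and its statistics section lists ten primary variables under one alpha of 0.05 with no rule for which decides the hypothesis

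*Protocol article*

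**What the plan says.** The Abstract (Methods) states: "The primary outcome measures are activity energy expenditure (doubly labeled water) and physical activity (accelerometry". It then continues: "Secondary measures will include resting metabolic rate via indirect calorimetry, use of time, maximal oxygen consumption".

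The last paragraph of the Background gives the primary aim as to "determine the effect of two different imposed 6-week exercise loads in previously sedentary 18–60 year olds on total energy expenditure and physical activity". The Abstract's background paragraph and the Discussion frame the aim in the same terms: total rather than activity energy expenditure.

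The Statistical analysis section opens its primary list with "The response variables for the primary analysis investigating the activitystat hypothesis will be total and activity energy expenditure derived from doubly labeled water". It adds "resting metabolic rate derived from indirect calorimetry, total counts and minutes spent in sedentary, light and MVPA derived from accelerometry", and closes with "minutes spent in MVPA, physical activity superdomain and physical activity level derived from the MARCA". Other use of time from the MARCA is assigned to the secondary analyses, along with anthropometry and physiology.

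On error control the section says "Alpha will be set at 0.05". The groups are compared through a time-by-group interaction. Further analyses at 50% and 75% compliance follow the completer analysis.

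**The concern.** A reader of the trial report needs to know in advance which result answers the question. Here the Abstract, the aim and the statistics section would give three different answers.

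The variables also need not agree. Imposed exercise can raise moderate-to-vigorous minutes while light activity falls and total expenditure stays flat. With ten variables labelled primary and no rule for combining them, some are likely to move and some not.

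The danger runs in both directions. A chance finding on one of ten could be reported as a real change. And because the activitystat predicts a stable total, a variable that fails to reach significance could be offered as evidence for the hypothesis. As listed, three summaries from a telephone recall also carry the same status as doubly labeled water, which the article itself calls the gold standard.

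**Working it through.** **1. The statements side by side**

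| Variable | Abstract, Methods | Stated aim | Statistical analysis |
|---|---|---|---|
| Total energy expenditure (doubly labeled water) | not listed | named | primary |
| Activity energy expenditure (doubly labeled water) | primary | not named | primary |
| Resting metabolic rate | secondary | not named | primary |
| Accelerometer: counts; sedentary, light and MVPA minutes | primary, variable not specified | physical activity, no instrument given | primary (4) |
| MARCA: MVPA, physical activity superdomain, activity level | not primary | physical activity, no instrument given | primary (3) |
| Other use of time (MARCA) | secondary | secondary aim | secondary |

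The count in the statistics section is 2 + 1 + 4 + 3 = 10. Resting metabolic rate and the three MARCA summaries are primary there but not in the Abstract. Total energy expenditure is in the aim but not among the Abstract's primary measures.

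**2. Family-wise error if all ten are tested at 0.05**

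The plan's own figure is the nominal 5%. For k independent tests with all nulls true, the chance of at least one false positive is 1 − 0.95^k.

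- k = 10: 1 − 0.95^10 = 1 − 0.599 = 40.1%.
- k = 2: 1 − 0.95^2 = 9.75%.

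The ten variables overlap, so independence gives the upper figure. The article states no correlations, so those below are assumptions. Simulation with 400,000 draws, using two-sided z tests and 2-df chi-square tests, gave for k = 10:

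| Assumed equal correlation | At least one false positive |
|---|---|
| 0.3 | about 35% |
| 0.5 | about 29% |
| 0.7 | 21–22% |
| 0.8 | 17–18% |
| 0.9 | about 13% |

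With correlation blocked by instrument (within/between from 0.5/0.2 to 0.8/0.5), the range was about 34% down to 24%.

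**3. The opposite direction**

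Suppose all ten effects were real and each test had 80% power. The chance that at least one misses significance is 1 − 0.8^10 = 1 − 0.107 = 89% if independent, and less under positive correlation. A null result to point to would therefore be common.

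**4. What two primary variables cost**

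Under Holm, the smaller p-value is tested at 0.025 and the other, if reached, at 0.05. The worst case for either variable is 0.025. By the normal approximation for a single contrast:

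- Power: Φ(1.960 + 0.842 − 2.241) = Φ(0.561) ≈ 71%.
- Sample-size ratio to keep 80%: [(2.241 + 0.842)/(1.960 + 0.842)]² = (3.083/2.802)² ≈ 1.21, so 26 per group becomes 26 × 1.21 = 31.5, rounded up to 32.

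The 26 per group is taken at face value. The article gives no endpoint, standard deviation or within-person correlation from which to derive it.

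**The case against.** The strongest reply has five parts.

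- **Two against ten compares unlike things.** The Abstract names measures by instrument; the statistics section names variables. Six of the ten (two from doubly labeled water, four from accelerometry) come from the Abstract's two instruments. This stands. The sharp conflict is over resting metabolic rate, the three MARCA summaries, and total versus activity energy expenditure. But an instrument with four variables and none chosen still does not fix a primary result.
- **Several variables are deliberate.** The Background asks for objective measures of both activity and energy expenditure, including resting metabolic rate, so that either candidate for the regulated quantity is monitored. That explains why they are measured. It does not explain why resting metabolic rate is secondary in one place and primary in another, nor why a recall is primary.
- **Adjustment may sit in an analysis plan that is not shown.** This is fair: the article does not literally say that each variable is tested at 0.05, and silence on adjustment would not be a finding alone. An unseen plan would still have to choose between statements that conflict in the article itself.
- **The 40% needs ten true nulls and independence.** This also stands. The programs are built to raise MVPA. If accelerometer MVPA, MARCA MVPA and the superdomain are expected to move, seven nulls remain and the independent figure is 1 − 0.95^7 = 30%. The excess over 5% remains.
- **A tighter alpha makes non-significance likelier**, which matters when a null can be read as support. This is a real cost and belongs in a restated power calculation.

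A reader might also infer that use of time as a whole switches from secondary to primary. It does not: only the three MARCA summaries do. Nor does the article support counting thirty primary tests (ten variables on completers and at two compliance levels). It presents the compliance analyses as subsequent ones, not as primary.

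**Conclusion.** The inconsistency is in the text and depends on no assumption: the Abstract, the aim and the statistics section define different primary sets. As written, the primary conclusion can be selected after the results are known, in favour of or against the activitystat.

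The error rate is conditional. If all ten are tested at 0.05 with all nulls true, it is at most about 40%, and about 35% to 13% at assumed equal correlations of 0.3 to 0.9, against 5% nominal. It would be wrong to quote 40% as the trial's actual false-positive rate. Even at an assumed correlation of 0.9, though, the rate is more than twice nominal. The primary set should be settled before any analysis.

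**What to change.** State one primary set, in the same words, in the Abstract, the aim and the Statistical analysis section:

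- Activity energy expenditure from doubly labeled water, as in the Abstract. Reword the aim to match and report total energy expenditure beside it.
- One named accelerometer variable, for example total counts.

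Test the two with Holm at family-wise 0.05. Move resting metabolic rate, the other accelerometer variables and all MARCA variables to secondary or supportive status, with estimates and confidence intervals. Label the 50% and 75% compliance analyses as sensitivity analyses.

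No measurement is dropped, and the change is one of wording except for power. A test with 80% power at 0.05 has about 71% in Holm's worst case, or needs about 32 rather than 26 per group. The planned 46 per group, less the anticipated 25% dropout, leaves 46 × 0.75 = 34.5. Extra recruitment may therefore not be needed if the 26 is sound, but the stated power should be recalculated for the two-primary test rather than assumed to carry over.

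### The recruitment target does not follow from its stated inputs: 26 per group with 25% dropout needs 35 per group (105), not 46 (138), and the abstract gives a third total, 146

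*Protocol article*

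**What the plan says.** The last paragraph of the Statistical analysis section gives the sample size as a chain of steps.

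- The power calculation: "sample of 26 participants per group (n=78) should be able to detect small to moderate effect sizes", at a 5% alpha level and 80% power.
- The allowance for loss and the conclusion drawn from it: "a dropout rate of 25% will be anticipated and therefore a total of 46 participants per group (n=138) will be recruited". The reasons given for the allowance are published dropout from physical activity interventions and the heavy assessment schedule.

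The Methods paragraph of the abstract gives a different total. It says that insufficiently active adults "will be recruited for this study (n=146"), and that "Participants will be randomly assigned to one of three groups".

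The same Statistical analysis section makes the main analysis per protocol, restricted to those who complete the intervention. It adds subsequent analyses at 50% and 75% compliance thresholds. Neither place mentions a second inflation factor or explains the difference between 138 and 146.

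**The concern.** The word linking the dropout rate to the target presents 46 as a derived number. A reader who repeats the step gets a much smaller one, and the gap is too large for rounding. The abstract, in the same future tense, then gives a different number to be recruited.

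Two things are at stake. First, the plan has no single recruitment total against which to judge whether recruitment was completed as intended. Second, because the main analysis keeps only completers, the expected loss after randomisation determines how many participants are analysed. The stated figures give either 34 or 26 completers per group, depending on which of them is believed, and the text does not say which was planned.

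**Working it through.** **Inputs** (Statistical analysis section unless noted)

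- Evaluable number required: 26 per group, 78 in total
- Anticipated dropout: 25%
- Stated target: 46 per group, 138 in total
- Total in the abstract: 146
- Groups: 3, of equal size as implied by 46 × 3 = 138

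The 26 is taken as given. It cannot be reproduced uniquely from the article, which gives the effect size only as a range ("d=0.2-0.6) for within groups (time effect) and group x time interactions") and states neither sidedness nor within-person correlation.

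**Step 1. Try to reproduce 46.**

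| Method | Per group | Rounded up | Total |
|---|---|---|---|
| Standard: 26 / (1 − 0.25) | 34.67 | 35 | 105 |
| Common shortcut: 26 × 1.25 | 32.5 | 33 | 99 |
| Shortcut applied twice: 26 × 1.25² | 40.6 | 41 | 123 |

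Inflating the total once, 78 / 0.75 = 104, makes no material difference. None of these gives 46 or 138.

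Two non-standard operations come close: 26 / 0.75² = 46.2, which is the 25% allowance applied twice, and 26 × 1.75 = 45.5, which rounds to 46. The article describes neither.

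**Step 2. Size of the gap.**

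- 138 − 105 = 33 participants; 138 / 105 = 1.31, so 31% above what the inputs require.
- 146 / 105 = 1.39, so 39% above.
- 146 − 138 = 8; 8 / 138 = 5.8% between the two stated totals.

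**Step 3. Forwards from the target at 25% dropout.**

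- 46 × 0.75 = 34.5, so about 34 completers per group.
- 146 × 0.75 = 109.5 completers in total.

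**Step 4. Backwards from the target to 26 per group.**

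- 1 − 26/46 = 43.5% loss.
- 1 − 78/146 = 46.6% loss.

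The stated rate is 25%.

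**Step 5. What 34 rather than 26 completers would mean.** For a given test, alpha and power, the smallest detectable standardised effect varies approximately with 1/√n. √(26/34) = 0.87, so it would be about 13% smaller at 34 completers per group than at 26.

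**The case against.** The strongest reply is that nothing is lost. Both totals are larger than the inputs require. At the stated 25% dropout, 46 per group leaves about 34 completers, more than the 26 that the article treats as sufficient. The model, outcomes and type I error are untouched, and the two totals differ by about 6%. All of this stands, and it limits the point to a reporting correction.

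The reply does not remove the error. The article prints the inputs, the inference and the result together, and they disagree. A fuller protocol could explain a missing step, but it could not make both 138 and 146 the planned number.

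Some stronger readings are tempting, but the document does not support them:

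- *The investigators really expected to lose about 43%, which would compromise a completers-only analysis.* The 43.5% is only a back-calculation; no such loss is stated. Applying 25% twice, for dropout and then for non-compliance, would nearly give 46. However, the compliance thresholds belong to the subsequent analyses, not to the main completer set, and no second allowance is mentioned.
- *The power statement is for the wrong number.* The 26 reads as a minimum evaluable number. Ending with 34 would not make a statement about 26 false.
- *146 must be wrong because it does not divide by three.* A total need not divide equally to be valid. What matters is that 146 and 138 are both given as the number to recruit.

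**Conclusion.** The point holds as an arithmetic and consistency error in a stated sample-size figure. With 26 evaluable per group and 25% dropout, the recruitment target is 35 per group (105), not 46 (138), and the abstract's 146 agrees with neither.

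A reader might infer that the trial is underpowered, or that 138 is right and 146 is the slip. Neither inference is supported. If 26 and 25% are correct, both stated totals are more than enough. The document does not show which of 26, 25%, 46 (138) or 146 is wrong. The conclusion assumes three equal groups and a single allowance for loss, as the text states, and accepts the 26 without verifying it.

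**What to change.** Give one recruitment total in the abstract and in the Statistical analysis section, and make the inputs agree with it by one of three routes:

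- (a) If 26 and 25% are as intended, correct the target to 35 per group (105 in total).
- (b) If 46 per group is intended, keep it, state that 25% dropout leaves about 34 completers per group, and give the power or detectable effect at that number.
- (c) If a further allowance was intended, for example to protect the compliance-threshold analyses, state it, its reason and the resulting total loss.

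The authors must choose the route, since the document does not settle it. If 146 is the intended total, the same reconciliation applies to that figure. The cost is wording in two places, with no extra participants and no change of design.
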